# Effect of He's* Santong* Needling Method on Dysphagia after Stroke: A Study Protocol for a Prospective Randomized Controlled Pilot Trial

**DOI:** 10.1155/2018/6126410

**Published:** 2018-08-14

## Abstract

**Background:**

Dysphagia is a common complication of stroke, affecting up to 78% of stroke patients. The existence of dysphagia after stroke has been associated with an increased risk for pulmonary complications and even mortality. Previous studies have shown that acupuncture could be potential therapeutic method for treatment of dysphagia after stroke. A prospective randomized controlled pilot trial is designed to evaluate the effect of He's* Santong* needling method on dysphagia after stroke.

**Methods and Design:**

Sixty eligible participants will be recruited and randomly assigned into treatment group (He's* Santong* needling method and swallowing rehabilitation training) and control group (swallowing rehabilitation training) in a 1:1 ratio. All treatments will be provided everyday on weekdays with a two-day interval at the weekend, during a total treatment course of four weeks. The Penetration-Aspiration Scale with Fiberoptic Endoscopic Examination of Swallowing will be assessed at baseline and endpoint (Week 4) as primary outcomes. The Saitoh's classification score, Swallowing-Related Quality of Life score, the Modified Mann Assessment of Swallowing Ability score, and Surface Electromyography will be evaluated at baseline and endpoint as secondary outcomes.

**Ethics and Dissemination:**

The trial protocol has been approved by the Research Ethical Committee of Beijing Hospital of Traditional Chinese Medicine Affiliated to Capital Medical University on 9 May 2017 (ethical batch number: 2017BL-013-02). Each participant will be notified regarding the study protocol. Written informed consent will be obtained from each participant.

**Trial Registration:**

ISRCTN registry: ISRCTN68981054; Registered on 25 September 2017.

## 1. Background

Dysphagia after stroke, manifested as difficulty in swallowing, is a common complication affecting between 37% and 78% of stroke patients [1]. Although the majority of patients achieve recovery from dysphagia spontaneously, dysphagia is still present in 11–50% of stroke sufferers at six months after stroke onset. Persistent dysphagia puts them at risk of pneumonia, malnutrition, dehydration, and even death [2]. It has been confirmed that the existence of dysphagia is associated with poor outcome during the subsequent years [3].

Swallowing is considered one of the most complex neuromuscular activities, which involves 26 pairs of muscles, five cranial nerves, and a complex neural network which coordinates swallowing muscles [4]. Sensory input from the oral cavity, pharynx, and larynx to the central pattern generator (CPG) has been shown to affect swallowing initiation, facilitation, and airway protection [5]. Dysphagia after stroke is thought to be due to damage to the swallowing-related cortex and subcortical structures. The recent researches have demonstrated that increased sensory input can drive long-term beneficial neural changes and reorganize brain plasticity of the swallowing cortex [6].

In order to improve the recovery and shorten the recovery time, various therapeutic options exist for dysphagia after stroke, including exercise-based rehabilitation, drugs, surgical rehabilitation, noninvasive brain stimulation (NBS), and neuromuscular electrical stimulation (NMES) [7]. There is no recommended routine clinical treatment for dysphagia after stroke, although several studies have shown that each approach appears to be promising [2, 7]. Effective alternative therapies are needed to be developed.

Acupuncture is widely utilized in interventions in complications after stroke in the Asia-Pacific region, although the specific mechanism remains to be further explored [8]. Previous studies found that acupuncture could improve the blood supply of vertebrobasilar artery and blood microcirculation in pseudobulbar palsy and regulate the connection of the cortex and the swallowing center of the brainstem to control swallowing reflection and coordinate motor movement of the swallow related muscles [9–11]. It is speculated that functional reconstruction of the neural network which coordinates swallowing-related muscles and nerves will lead to swallowing recovery [5]. According to traditional Chinese medical theory, acupuncture treatment performs function by the regulation of Qi and blood of swallowing-related meridian and collateral. Three meta-analysis researches have indicated that acupuncture may have a beneficial positive effect on dysphagia after stroke [12–14].

In clinical practice, acupuncture is often combined with other therapeutic stimuli, the so-called combined acupuncture technique, which has been widely used to enhance the acupuncture effect. He's Santong needling method is a combined acupuncture technique, which is often applied to complications after stroke [15]. Compared with ordinary acupuncture, He's Santong needling method has a synergistic effect of three acupuncture techniques: Weitong (normal needling), Wentong (fire needling), and Qiangtong (bloodletting) [16]. The procedures of Weitong method are very similar to ordinary acupuncture, which is well known in the western world. However, most western physicians are not familiar with Wentong (fire needling) and Qiangtong (bloodletting) [17]. Fire needling is an acupuncture technique involving the swift pricking of acupuncture points or certain areas of body with a red-hot needle made of manganese and tungsten alloy [18]. This technique provides the patients with both mechanical stimulation and thermal stimulation, so it is regarded as a combination of acupuncture with thermal stimulation which warm up the meridian to harmonize the Qi and blood with the heat of the fire needling [19]. Some reports have shown that the therapeutic effect of fire needle is superior to ordinary acupuncture on several diseases including acute cerebral infarction [20–22]. It is believed that fire needling has a synergistic effect of heat from the red-hot needle and stimulation on acupuncture points or the certain areas of body in improving blood circulation and eliminating blood stasis [23]. Bloodletting, known as pricking bloodletting method, is a therapeutic acupuncture technique where a small amount of blood from a superficial vein is released with a three-edged needle [18]. It is thought that pricking superficial vein for bloodletting can dredge the meridians and collaterals and promote blood circulation to remove stasis. Therefore, bloodletting has been applied in various types of diseases including stroke for thousands of years in China. Previous study revealed that bloodletting increased the cerebral blood flow in ischemic patients which might improve local microcirculation and prevent neuron apoptosis [24].

Thus, we hypothesize that He's Santong needling method is beneficial to dysphagia after stroke. We design a prospective randomized controlled pilot trial to investigate the effect of He's Santong needling method on dysphagia after stroke.

## 2. Methods

### 2.1. Study Design

A prospective randomized controlled pilot trial is designed to evaluate the effect of He's* Santong* needling method on dysphagia after stroke. Sixty participants with dysphagia after stroke will be randomly assigned to the treatment group (He's* Santong *needling and swallowing rehabilitation training) and control group (swallowing rehabilitation training) at a 1:1 ratio. The schedule of enrolment, interventions, and assessments is summarized in Table 1, and the flow diagram of the study procedure is presented in Figure 1.

### 2.2. Recruitment

Trial participants with dysphagia after stroke are being recruited by clinicians from Acupuncture and Moxibustion wards at the Beijing Hospital of Traditional Chinese Medicine Affiliated to Capital Medical University. Meanwhile, information flyers introducing the details of the trial are being posted at the inpatient and outpatient clinics for greater exposure.

### 2.3. Study Procedure

The treatment is performed 5 days a week for 4 weeks. Once potential participants show interest in this trial, they will be invited to attend an eligibility assessment in which their eligibility will be assessed by trial investigators; thereafter, eligible participants will be enrolled and randomly assigned to either the treatment group or the control group and given a 4-week treatment.

### 2.4. Participants

#### 2.4.1. Inclusion Criteria

Participants who meet all of the following requirements will be allowed for enrolment: (1) aged between 18 and 80 years old, (2) diagnosed as having ischemic stroke which confirmed by a CT or MRI scan, (3) identified as clinical dysphagia using Kubota water swallowing test (level 3, 4, or 5), (4) the symptoms of dysphagia lasting over two weeks to three months after stroke onset, and (5) absence of cognitive impairment (score of the abbreviated mental test (AMT) >=8).

#### 2.4.2. Exclusion Criteria

Patients will be excluded if they have (1) presence of dysphagia before stroke, (2) progressive neurological disorder, (3) serious psychological disorder, (4) a history of pacemaker implantation, (5) unstable cardiopulmonary status, and (6) pregnancy, lactation, or insufficient contraception.

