### 2.6. Blinding and Informed Consent

In this study, the participants will be informed that they have a 50% chance of being allocated in either of the two groups: He's* Santong* needling method plus swallowing rehabilitation training in the treatment group and swallowing rehabilitation training in the control group. Hence participants will not be blinded to their group allocation. Furthermore, it is unfeasible to blind the acupuncturist because of the nature of the intervention; they will be required to minimize communication with participants or outcome assessor regarding treatment procedures and responses. However, outcome assessors and statisticians will be blind to allocation throughout the entire trial.

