### 2.7. Interventions

The acupuncture points were determined according to records in ancient and modern books and results of previous research on acupuncture treatment for dysphagia after stroke [14]. All participants will go through a standardised interview and will be provided with details of the study. The acupuncturist who deliver treatments for treatment group are registered with the Ministry of Health of the People's Republic of China as Chinese medicine practitioners and have more than 20 years clinical experience. Before the trial begins, all acupuncturists will receive special training regarding the purpose and standard procedure of the trial, treatment strategies, and quality control. The treatment details will be fully documented in accordance with the Standard Protocol Items for Randomized Trials (STRICTA) and good clinical practice guidelines [25].

All participants will receive 4-week therapy for five sessions each week. In the treatment group, participants will receive He's* Santong* needling method and swallowing rehabilitation training. In the control group, participants will be treated with swallowing rehabilitation training.

He's* Santong* needling method has three acupuncture procedures:* Weitong* (normal needling),* Wentong* (fire needling), and* Qiangtong* (bloodletting). The* Weitong *procedure will be received five sessions every week, and the* Wentong* and* Qiangtong* procedure will be given two sessions per week on weekdays.

The swallowing rehabilitation training consists of indirect behavioral exercises (e.g., appropriate dietary modification) and direct behavioral exercises (e.g., effortful swallowing and supraglottic swallow technique) according to the Chinese expert consensus for stroke rehabilitation evaluation and treatment, under the direction of rehabilitation practitioners [26]. The 30-minute swallowing rehabilitation session will be carried out by the same rehabilitation practitioner for each participant.

Both groups will receive secondary prevention of ischemic stroke including antiplatelet, antihypertensive, and hypolipidemic therapy according to Chinese Guidelines for Diagnosis and Treatment of Acute Ischemic Stroke [27].

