#### 2.7.1. The Acupuncture Points Used in He's Santong Needling Method

*(1) Weitong (Normal Needling)*. The points in the* Weitong *procedure (needle retention for 30 minutes) are bilateral GB20 (Fengchi), GV16 (Fengfu), TE17 (Yifeng), CV23 (Lianquan), Jialianquan, ST40 (Fenglong), and HT5 (Tongli) (see Figure 2).

All needles will be inserted 10 to 15 mm in depth and manually manipulated with rotation methods to produce a characteristic sensation known as De Qi (feeling of needle sensation that refers to the tenseness around the needle felt by the practitioner and numbness, distension, soreness, and heaviness around the point felt by the participant).

*(2) Wentong (Fire Needling)*. The points in the* Wentong *procedure are bilateral GB20 (Fengchi) and CV23 (Lianquan) (see Figure 2).

The fire needle used in this study is made of manganese and tungsten alloy which will maintain hardness at high temperatures. When the fire needle has been burnt red-hot over a spirited lamp, the acupuncturist will insert the red-hot needle into GB20 and CV23 to a depth of 10mm and then withdraw swiftly without needle retention. The needle hole will be pressed with a sterilized dry cotton-ball [28].

*(3) Qiangtong (Bloodletting)*. The points in the* Qiangtong *procedure are EX-HN12 (Jinjin), EX-HN13 (Yuye), and Yanhoubi (see Figure 2)

Before bloodletting on EX-HN12 and EX-HN13, the acupuncturist will raise the tongue with a spatula and stab the sublingual veins to release 1-2 drops of blood with a three-edged needle after strict disinfection. When performing on the Yanhoubi, the acupuncturist will keep the participant's mouth open with a retainer and press the tongue with a spatula and release 1-2 drops of blood from the pharynx posterior wall with a three-edged needle after strict disinfection [28].

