### 2.9. Safety Assessment

All adverse events (AEs) during the treatment will be recorded on AE case report in detail, such as time of appearance, intensity of AEs, and possible causes. The investigators will collect information about AEs and assess whether the AEs are associated with the techniques of acupuncture treatment. Participants will be interviewed about any abnormal reactions or feelings. Participants encountering with mild or moderate AEs will be treated according to their symptoms. Severe AEs will be reported to the Research Ethics Committee, which will provide medical advice to the research team within 48 hours, and the Research Ethics Committee will determine whether a termination of the trial is required.

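### The eligibility criteria have no bleeding-risk exclusion, although the treatment arm has the mouth and pharynx pricked twice weekly in dysphagic patients whose background care includes antiplatelet therapy

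*Protocol article*

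**What the plan says.** Section 2.4.1 introduces five numbered inclusion criteria with "Participants who meet all of the following requirements will be allowed for enrolment". They cover age, ischaemic stroke confirmed by imaging, dysphagia at Kubota level 3 to 5, duration of symptoms, and cognition. Section 2.4.2 gives six numbered exclusions. It begins "Patients will be excluded if they have (1) presence of dysphagia before stroke, (2) progressive neurological disorder, (3) serious psychological disorder" and ends with pacemaker, unstable cardiopulmonary status, and pregnancy, lactation or inadequate contraception.

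Section 2.7.1 describes the bloodletting component. At EX-HN12 and EX-HN13 the acupuncturist is to "stab the sublingual veins to release 1-2 drops of blood with a three-edged needle after strict disinfection". At Yanhoubi the instruction is to "release 1-2 drops of blood from the pharynx posterior wall with a three-edged needle". Section 2.7 sets the frequency of fire needling and bloodletting: the "procedure will be given two sessions per week on weekdays", within a 4-week course. The same section states: "Both groups will receive secondary prevention of ischemic stroke including antiplatelet, antihypertensive, and hypolipidemic therapy".

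On harm, section 2.9 provides for recording adverse events and adds: "Severe AEs will be reported to the Research Ethics Committee, which will provide medical advice to the research team within 48 hours". Section 3.2 cites national standards for carrying out the techniques.

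**The concern.** Bleeding is the most obvious hazard specific to this procedure, and the population is poorly placed to tolerate it. Impaired swallowing is the condition under study, and the primary outcome grades penetration and aspiration. A patient with both impaired clotting and impaired airway protection could bleed, or aspirate blood, after a pharyngeal pricking.

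The control arm receives no needling, so any such event would fall on one arm only. With 30 patients per arm, a single serious bleed would weigh heavily on what the pilot can say about safety, and it could lead to withdrawal from the treatment arm. The criteria screen for pacemakers and contraception but not for this.

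**Working it through.** **1. Eligibility lists against the intervention**

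| Element | Where | Content |
|---|---|---|
| Inclusions | 2.4.1 | Five items, none on bleeding risk. Stroke must be ischaemic, with no limit on subtype or concomitant drugs |
| Exclusions | 2.4.2 | Six items, none on bleeding disorder, platelets or anticoagulants. Item (5) covers only unstable cardiopulmonary status |
| Sites pricked | 2.7.1 | Sublingual veins (EX-HN12, EX-HN13) and posterior pharyngeal wall (Yanhoubi) |
| Background drugs | 2.7 | Antiplatelet therapy is part of secondary prevention in both groups |

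No clause allows exclusion at the investigator's discretion. A stable patient who is anticoagulated or thrombocytopenic therefore meets the criteria as printed.

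**2. Do the stated safeguards fill the gap?**

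- Practitioner experience and training (2.7) govern delivery.
- The 1-2 drop target and the disinfection (2.7.1) govern technique.
- Adverse event recording and reporting (2.9) act after harm has occurred.
- The national standards (3.2) are described as standardising manipulation.

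As described, none of these decides who may be enrolled.

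**3. Exposure per treated participant**

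- Sessions: 2 per week × 4 weeks = 8.
- Prickings, assuming one per named site per session: 8 × 2 sublingual = 16, and 8 × 1 pharyngeal = 8, giving 24.
- Sessions across the arm: 8 × 30 = 240.

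**4. Chance that an at-risk entrant is needled**

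The plan's total reproduces as 2 × 30 = 60. Under 1:1 allocation participants are told that "they have a 50% chance of being allocated in either of the two groups". Let k be the number of at-risk patients among the 60. The document does not give k, so it is an assumption. Ignoring blocks, the chance that at least one is among the 30 in the treatment arm is 1 − C(30,k)/C(60,k):

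- k = 1: 1 − 30/60 = 0.50
- k = 2: 1 − 435/1770 = 0.754
- k = 3: 1 − 4060/34220 = 0.881

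**5. What the pilot could learn by watching for events instead**

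The document gives no bleeding rate, so this step is illustrative. If no bleeding event occurred among 30 treated patients, the one-sided 95% upper limit for the risk would be 1 − 0.05^(1/30) = 0.095, or 9.5%. For assumed per-patient risks p of 1%, 2%, 5% and 10%, the chance of at least one event in 30, 1 − (1 − p)^30, is 26%, 45%, 79% and 96%. A clean record in this pilot would therefore not show that the procedure is safe.

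**The case against.** The strongest reply is that this is a journal article condensing a protocol approved by an ethics committee. A fuller document might hold further exclusions, and section 2.3 has investigators assess each candidate. The national standards might also list contraindications, which cannot be checked here. This lowers confidence but does not remove the point. The article prints numbered, closed eligibility lists, which are not the kind of detail an article usually leaves out, and nothing in it makes the standards a condition of enrolment.

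A second reply is that the only bleeding-risk factor the document names is antiplatelet therapy, which the proposed fix leaves in place. That is so, and deliberate. Antiplatelet drugs are part of the trial's own background care, so excluding patients on them would remove much of the population the trial is meant to study. The fix targets patients with a further clotting impairment on top of that. It is true that nothing in the document shows such patients will be recruited; the criteria simply do not keep them out.

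Third, the allocation chances measure exposure and not harm, the count of 24 assumes one pricking per site, and the intended volume is only 1-2 drops. All three statements are correct. But the intended volume does not guarantee that bleeding stops there when clotting is impaired.

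Fourth, no formal between-arm safety comparison is specified, and harms confined to the treated arm are inherent in an add-on design. That also stands. The point is preventable harm to participants, not bias in the efficacy estimate.

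**Conclusion.** The concern holds. Followed as written, the plan admits a stable patient with a bleeding disorder, low platelets or therapeutic anticoagulation to repeated pricking of the mouth and pharynx. If allocated to treatment, such a patient would have 8 sessions and about 24 prickings. The chance that at least one is so allocated is 50%, 75% or 88% for an assumed 1, 2 or 3 such entrants. How many would actually enter, and how often they would bleed, is unknown from the document.

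This is an eligibility and safety matter that should be corrected. It does not change the sample size, significance level or power. Confidence is medium, because a full protocol that is not shown could contain the missing criterion.

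**What to change.** Add to section 2.4.2: '(7) known bleeding disorder, clinically significant thrombocytopenia, or current therapeutic anticoagulation'. Check it from medication history and routine laboratory values before randomisation, and apply it to both arms. The sponsor's clinicians should set the platelet threshold. State that antiplatelet therapy alone does not exclude a patient. The pacemaker criterion needs no change.

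A pre-procedure check with a rule for withholding bloodletting would also protect patients, but it is weaker. It acts after randomisation and in one arm only, and it removes one of the three components under test. Under intention-to-treat, patients who miss that component would dilute the comparison. If they were dropped from the per-protocol set, the loss would be from one arm only.

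The cost is one added eligibility line, a few otherwise eligible patients lost, and a slightly narrower ischaemic-stroke population.

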### 2.5. Randomization and Allocation Concealment

The Research Centre of Clinical Epidemiology, Peking University Third Hospital, will be responsible for random program. A block randomization method (with a block size of four) will be used to generate the random allocation sequence; predetermined computer-made randomization opaque sealed envelope will be used to ensure the allocation concealment. According to the serial number of participant, a numbered envelope contains the group assignment will be opened.

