### 2.11. Sample Size

This pilot study is to evaluate the effect of He's* Santong* needling method on dysphagia after stroke. However, no previous study was found on the effect of acupuncture on the PAS with FEES. A sample size of 30 per group was regarded as a reasonable minimum recommendation for a pilot study [36]. Therefore, we plan to recruit 60 participants.

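### A single, published block size of four could let a recruiter who tracks earlier assignments know about one third of allocations in advance

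*Protocol article*

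**What the plan says.** Section 2.5 of the protocol article fixes the method: "A block randomization method (with a block size of four) will be used to generate the random allocation sequence". An external research centre "will be responsible for random program". Concealment relies on opaque sealed envelopes taken in order: "According to the serial number of participant, a numbered envelope contains the group assignment will be opened". This reads as one running sequence. The article mentions no stratification factor and no variation in block size.

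Section 2.2 says that participants "are being recruited by clinicians from Acupuncture and Moxibustion wards" of a single hospital, in the present tense, in an article dated 14 August 2018. Flyers in the inpatient and outpatient clinics support recruitment. Section 2.6 states: "Hence participants will not be blinded to their group allocation". It also says that the acupuncturists cannot be blinded. Those named as blinded are the outcome assessors and the statisticians; recruiting clinicians are not among them.

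**The concern.** A sealed envelope hides the next assignment only from someone who cannot work it out. With a constant block of four and 1:1 allocation, each block holds two assignments to each arm. Once one arm has been used up in the block, the rest of that block is known without touching an envelope. The arms are easy to tell apart (needling, fire needling and bloodletting against none), and the recruiters come from the acupuncture wards, so earlier assignments may well be visible to them.

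A recruiter who can foresee the next assignment can bring a patient forward, delay one or pass one over without breaking any eligibility rule. Section 2.4.1 leaves room for this: it admits three levels of the water swallowing test and onset from two weeks to three months earlier. Section 1 says that most patients recover spontaneously, so the timing of enrolment probably carries prognostic information. Bias of this kind arises before any outcome is measured, so blinded rating of the primary outcome does not remove it.

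**Working it through.** **Inputs**
- Block size 4 (Section 2.5).
- 1:1 allocation: "control group (swallowing rehabilitation training) at a 1:1 ratio" (Section 2.1), so two per arm in each block.
- Total: "Therefore, we plan to recruit 60 participants" (Section 2.11).

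**The plan's own figure.** 2 × 30 = 60, as stated, and 60 / 4 = 15 whole blocks. The article gives no figure for predictability, so there is none to reproduce.

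**Allocations known with certainty.** The six equally likely blocks are AABB, ABAB, ABBA, BAAB, BABA and BBAA. An assignment is certain when the earlier ones in its block have used up one arm.

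| Position | Probability that it is certain | Reason |
|---|---|---|
| 1 | 0 | nothing used |
| 2 | 0 | both arms remain |
| 3 | 2/6 = 1/3 | only after AA or BB |
| 4 | 1 | always |

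- Expected per block: 1/3 + 1 = 4/3, which is (4/3)/4 = 33.3% of allocations.
- Over 15 blocks: 15 × 4/3 = 20 of 60.
- Spread: a block gives 1 certain allocation with probability 4/6 and 2 with probability 2/6, so the variance is (1/3)(2/3) = 2/9. Over 15 blocks the SD is √(15 × 2/9) = 1.83. The limits are 15 × 1 = 15 (25%) and 15 × 2 = 30 (50%). By exact convolution, 17 to 23 covers about 95% of sequences.

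**Best guess.** Guess the arm with more places left in the block, and toss a coin when they are equal.
- Position 1: 1/2. Position 2: 2/3. Position 3: (1/3)(1) + (2/3)(1/2) = 2/3. Position 4: 1.
- Sum: 1/2 + 2/3 + 2/3 + 1 = 17/6 of 4, or 70.8%. Over 15 blocks: 15 × 17/6 = 42.5 of 60, against 30 of 60 by chance.

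**How the size depends on the assumptions**
- Block size known only for the last m whole blocks: the expected number is 4m/3. For m = 5, 10 and 15 this gives 6.7, 13.3 and 20.
- One of the first three assignments in a block missed: the fourth stays certain only if the two that were seen match, which has probability 1/3.

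**Effect of varying the block size.** Sizes were drawn at random and concealed, with 3,000 simulated sequences of 60. The recruiter was assumed to know the set of sizes and the full history.

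| Block sizes | Known with certainty | Best guess correct |
|---|---|---|
| 4 only (exact) | 33.3% | 70.8% |
| 4 and 6 | 5.6% | 69.1% |
| 2, 4 and 6 | 4.1% | 70.0% |
| 4, 6 and 8 | 2.2% | 67.8% |

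**The case against.** The strongest reply is that the one-third figure is conditional. It needs a recruiter who knows the block size and has followed each earlier assignment in the current block. The article states neither for the recruiting clinicians. It does not say that they deliver the acupuncture, open the envelopes or see the sequence. Section 2.2 speaks of more than one ward, Section 2.3 gives the eligibility assessment to trial investigators, and the list is generated outside the hospital. This stands. That the wards see earlier assignments is a fair inference from one hospital, one sequence and visibly different arms, but it is an inference.

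The timing objection also stands. Recruitment was under way when the article appeared, so publication can expose only participants randomised afterwards, and the article does not give their number. Nothing shows that the wards knew the block size before then.

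That no strata exist rests on the silence of a condensed article. If there were strata, each complete block within a stratum would still give 4/3 certain assignments on average, though incomplete blocks and harder tracking would lower the total.

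External generation and numbered opaque envelopes are real safeguards, and a small fixed block keeps the groups almost equal in a trial of 60. They do not stop deduction from a known constant block.

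That this is a pilot is a weaker reply. Section 2.11 gives the purpose as evaluating the effect, and Section 2.12 plans significance tests at 0.05.

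**Conclusion.** The point holds as a design vulnerability that is cheap to reduce. If a recruiter knows the block size and tracks the current block from the first participant, 20 of 60 allocations are certain in expectation, with limits of 15 and 30. With later knowledge or incomplete tracking the number is smaller. The arithmetic is exact; how far its conditions are met cannot be judged from the article.

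A reader might infer more than the document supports:
- That one third of allocations are in fact predictable to the recruiting ward, or that selection has taken place. The article shows neither.
- That any bias would be beyond repair by adjustment. Severity is measured at baseline, so adjustment could remove the part due to measured severity. Selection on unmeasured prognosis would remain.
- That the 71% guessing rate is a harm that varying blocks would cure. It barely moves; the gain lies in removing certainty.
- That envelopes are opened before baseline assessment, or that the registry discloses the block size. Table 1 puts consent, allocation and baseline assessments in one column without an order, and nothing is said about what the registry entry contains.

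**What to change.** If envelopes remain unopened, the independent randomisation centre should regenerate the rest of the list with randomly varying block sizes, for example 4 and 6. The sizes and their order should be kept from recruiting staff until recruitment ends. The change and its date should be documented. Certain predictions fall from 33.3% to about 5.6%, or from 20 to about 0.056 × 60 = 3.4 if applied to all 60, even if the set of sizes becomes known.

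The cost is one new list, new envelopes and a possible small imbalance. If the switch is made at the end of a complete block, only a truncated last block can unbalance the groups. Stopped after two or four assignments, a block of 4 or 6 leaves the arms at most two apart (2:0 or 3:1), so the worst result at 60 is 31 against 29.

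If recruitment is already complete, nothing can be changed in the allocation. The report should then state the fixed block size, say who could see earlier assignments, and name the predictability as a limitation.
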